### Treatment regimens

#### Control group

Control group participants are sent an information booklet about the prevention of diabetes.

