#### Intervention group

Participants randomised to the intervention group are invited to participate in the Baby Steps programme. This has two components: a group-based structured education programme and a secure mobile web application which provides access to information and learning tools to supplement the group programme.

The group programme is based on Let’s Prevent Diabetes and Walking Away from Diabetes, group education programmes which have been shown to be effective for people at increased risk of developing T2D [38, 39]. They are based on robust theoretical frameworks and the philosophy is based on patient empowerment [40–42]. The Baby Steps programme comprises two group sessions that are each 3 h long and are delivered approximately two weeks apart. A total of 8–10 people are booked to attend each programme and are given the opportunity to bring a friend or member of the family if they wish. Session 1 focuses on the background to GDM and being at risk of T2D, physical activity and other modifiable risk factors and goal setting (Table 1). The second session revisits physical activity and reviews progress on goals, barriers and solutions and then covers diet and food choices with goal setting relating to reducing risk of developing T2D. The programme is delivered in a facilitative style that encourages participation with the use of reflective questioning and problem-solving activities to promote engagement. The education sessions are delivered at the two hospital sites as well as at local community venues. The target is to attend within two months of recruitment. However, a pragmatic approach is taken and this is not always possible. A sensitivity analysis will be performed to take this into account.

**Table 1 Tab1:** Contents of the Baby Steps group education programme

Session 1	Session 2
Introduction and housekeeping (5 min)	Welcome back (5 min)
Your story (25 min)	Sharing stories (30 min)
Blood glucose (20 min)	Revisiting physical activity (15 min)
How could being at risk of diabetes affect my health? (15 min)	Weight management (30 min)
Risk story (25 min)	Food choices (45 min)
Being more active (70 min)	Planning to reduce my risk (30 min)
Reflections (5 min)	Questions and future care (10 min)
TOTAL - 2 h 45 min (+ 15 min break) = 3 h	TOTAL - 2 h 45 min (+ 15 min break) = 3 h

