During Session 1, participants are given a secure link to a mobile web application which has been developed to accompany the programme. The application has two main functions: first, to provide an interactive education component to follow on from the group component; and second, to motivate the user into becoming more active. It contains a variety of resources of different formats (e.g. video animations, expert videos, interactive activities and quizzes) which supplement the messages delivered during the group sessions. In addition, there are booster sessions (released monthly for nine months) which contain further information and challenges. Participants are given a wrist-worn activity monitor that can connect to the website using a human application programming interface (API). Regular automated messages are sent in relation to goal setting, goals achieved and the setting of new challenges with daily updates and motivational messages. Participants can opt to join a group who can use the website to share their challenges and experiences with their peers. More information on the application is provided in Additional file 2.

Development of the group education programme followed an iterative pathway comprising various stages of design, testing and refining the programme [43]. It was developed by a multidisciplinary team with substantial co-production from patient and public involvement (PPI) and other stakeholder groups (including midwives and maternity care assistants). Four meetings were held with stakeholders (two with women who had previously had GDM and two with healthcare professionals). The discussions were led by an independent and experienced qualitative researcher from the University of Leicester and informed on content of the programme, the online resource and practical issues such as the number of sessions, ideal venues and times of the day, and whether the session should be limited to women. The interactive website is hosted on a safe secure server and was developed in collaboration with a web designer with healthcare professionals and patient groups involved at all stages. An iterative pathway similar to that used in the development of the group programme was followed.

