### Statistical analysis

Descriptive characteristics at baseline will be summarised by treatment arm. Numbers (with percentages) for binary and categorical variables and means (and standard deviations) or medians (with lower and upper quartiles) as appropriate for continuous variables will be presented. Preliminary graphical and tabular presentations of the data will be inspected for the correct statistical modelling assumptions.

The primary analyses will use a complete case population. For the primary outcome (change from baseline in total physical activity), treatment arms will be compared using linear regression with a binary indicator for randomisation group as the explanatory variable, terms for the stratification factors as confounders, and adjustment for the change in accelerometer wear time and baseline total physical activity. Sensitivity analyses will include a per-protocol analysis (defined as attending at least one of the two group education sessions, i.e. those randomised to intervention but not attending either group session will be excluded) and an intention-to-treat analysis where missing data will be imputed using multiple imputations. Interaction effects will be fitted between intervention arm and age (< median vs ≥ median), and ethnicity (White European vs other). If the interaction term is statistically significant then stratified analyses will be performed for that factor using the same model as the primary analyses. Secondary outcomes will be analysed using similar methods as the main analysis, with an appropriate model selected dependent on the distribution of the outcome.

The results of all comparative analyses will be presented with 95% confidence intervals and statistical significance for main effects will be assessed at the 5% level. All *p* values shown will be two-sided. Statistical significance for interaction effects will be assessed at the 10% level.

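### The per-protocol sensitivity analysis drops non-attenders from the intervention arm only, so it compares women selected on attendance with controls who are not

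*Protocol article*

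**What the plan says.** All references are to the protocol article.

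- **Statistical analysis** sets the main comparison by randomised group: "The primary analyses will use a complete case population". The linear regression has terms for the stratification factors and "adjustment for the change in accelerometer wear time and baseline total physical activity".
- The same section adds: "Sensitivity analyses will include a per-protocol analysis". It is a "per-protocol analysis (defined as attending at least one of the two group education sessions", and the rule is spelled out: "those randomised to intervention but not attending either group session will be excluded". An intention-to-treat analysis with multiple imputation is listed beside it, also as a sensitivity analysis.
- **Control group** describes all that the other arm is stated to get: "Control group participants are sent an information booklet about the prevention of diabetes". Attendance at a session is not defined for these women.
- **Intervention group** makes attendance a response to an invitation that follows randomisation.

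No expected attendance is given, and no method that keeps the randomised comparison is named for the question of uptake.

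**The concern.** The exclusion acts on behaviour after randomisation and in one arm only. Women who would not have come remain among the controls, because nobody can identify them there, while their counterparts are removed from the intervention arm. The two groups then differ in composition as well as in treatment.

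A per-protocol estimate is normally read as the effect in women who took up the programme. Here it adds to that effect any difference between attenders and non-attenders that the covariates do not capture. The practical risk is a null or borderline primary result next to a larger, nominally significant per-protocol result, read as evidence that the programme works in those who attend. The section on statistical analysis gives all comparative results confidence intervals and tests main effects at 5%, so nothing in the reporting rules would mark this estimate as different in kind.

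**Working it through.** **1. The plan's own figure.** Inputs from Sample size: difference 2.1 mg, SD 5.3 mg, power 80%, significance level 5% (two-sided, from Statistical analysis). The two-sample t-test calculation gives 100.96, so 101 per arm and 202 in total, as stated. Then 202 / (1 − 0.30) = 288.6, or 289, against 290 planned. The sample size reproduces and is not in question. It supplies the scale: 101 evaluable women per arm and a 2.1 mg target.

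**2. The bias.** Let a be attendance among analysed intervention women. With no programme effect, let A and B be the mean adjusted change in would-be attenders and would-be non-attenders, and d = A − B.

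- Controls hold both kinds: mean = aA + (1 − a)B.
- Intervention women kept per protocol: mean = A.
- Difference = A − aA − (1 − a)B = (1 − a)d.

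Illustration (both inputs assumed): a = 0.75 and d = 2 mg give 0.25 × 2 = 0.5 mg, and 0.5 / 2.1 = 24%.

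**3. Range.** Neither a nor d is in the documents, so every row and column below is an assumption. The last column is the two-sided rejection rate under no effect at d = +2.1, by normal approximation. It uses SE = √[(5.3² − q(1 − q)d²)/(101(1 − q)) + 5.3²/101], with q = 1 − a.

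| Non-attendance q | d = −1.0 | d = 0 | d = +1.0 | d = +2.1 | Rejection at d = +2.1 |
|---|---|---|---|---|---|
| 10% | −0.10 | 0 | 0.10 | 0.21 | 5.9% |
| 20% | −0.20 | 0 | 0.20 | 0.42 | 8.3% |
| 30% | −0.30 | 0 | 0.30 | 0.63 | 12.1% |
| 40% | −0.40 | 0 | 0.40 | 0.84 | 16.7% |

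**4. Does the planned adjustment remove it?** This was simulated under no effect with 202 women, 4,000 replicates and adjustment for baseline activity, at 20%, 30% and 40% non-attendance.

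- Attendance depends on baseline activity only: mean shift about 0, rejection about 5%.
- Attendance also depends on an unmeasured trait that raises later activity: shift +0.44, +0.64 and +0.84 mg; rejection 8.7%, 11.5% and 17.5%.
- Attendance depends on an unmeasured trait that lowers later activity: shift −0.51, −0.74 and −0.99 mg.
- All women analysed as randomised: rejection about 5% throughout.

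**5. With a real effect.** Suppose the effect is E = 2.1 mg in attenders and nil in non-attenders, with q = 30%. The arm difference as randomised is 0.70 × 2.1 = 1.47 mg. The per-protocol estimate is 2.1 + 0.30d, which is 2.40 mg at d = 1 and 2.73 mg at d = 2.1. The complier-average estimate is 1.47 / 0.70 = 2.1 mg whatever d is.

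**6. Price in precision.** At a = 0.75, ignoring covariates, the complier-average SE is about 5.3 × √(2/101) / 0.75 = 0.746 / 0.75 = 0.99 mg. The naive per-protocol SE is 5.3 × √(1/101 + 1/75.75) = 0.81 mg. The interval is wider by a factor of about 0.99 / 0.81 = 1.2.

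**The case against.** The strongest reply is that this is one pre-specified, openly defined sensitivity analysis. The primary analysis compares randomised groups, an intention-to-treat analysis is also planned, and no claim of success hangs on the per-protocol result. All of that stands and limits the importance of the point. It does not make the contrast a randomised one.

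The second reply is that direction and size are unknown. That also stands. The Background names lack of time, work and family demands, and childcare as barriers. It is reasonable to expect that these reduce both attendance and later activity, but the documents do not show a worse adjusted change in non-attenders. A reader might infer that the analysis must flatter the programme; the documents support only that it can be biased, in either direction.

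Two further inferences are tempting and are not supported:

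- **Late attendance.** Where sessions are not attended within the two-month target, the article says only "A sensitivity analysis will be performed to take this into account". It does not say that late attenders will be dropped, so the same flaw cannot be attributed to an unstated method.
- **Attending Session 2 only.** The article says "During Session 1, participants are given a secure link to a mobile web application", but not that a woman who misses that session is refused the link. No number of such women is given, so misclassified exposure is a conjecture.

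The proposed remedy has an assumption of its own. Randomised arm must affect activity only through attendance. Participants are unblinded, intervention women are telephoned about dates, and only controls are stated to receive the booklet, so non-attenders might differ slightly by arm. The assumption has to be stated. Narrower exposures make it worse. If 75% attended, 50% within two months, and all attenders had effect E, taking on-time attendance as the exposure would give 0.75E / 0.50 = 1.5E, because late attenders counted as unexposed still received the programme. Taking Session 1 attendance as the exposure has the same problem.

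**Conclusion.** The point holds for the per-protocol sensitivity analysis and only for that. The stated rule removes non-attenders from one arm, no matching exclusion is possible among controls, and the planned covariates cure the problem only if attendance depends on nothing else that predicts change in activity. The bias is (1 − attendance) × (attender minus non-attender difference in adjusted change). The 0.5 mg figure (24% of the target) illustrates the scale under assumed inputs and is not an estimate for this trial. The primary analysis, the multiple-imputation analysis and the sample size are untouched. Importance is low to moderate: the correction is cheap and mainly prevents a misreading of the results.

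**What to change.** In Statistical analysis, replace the per-protocol analysis, or accompany it, with a complier-average causal effect by two-stage least squares:

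- instrument: randomised arm;
- exposure: attended one or more group sessions, the definition already in use;
- covariates: those of the primary model.

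State the exclusion restriction as an assumption and name its weak spots: lack of blinding, the telephone contact in the intervention arm, and the booklet stated for controls only. State also that no control is assumed to attend. If the per-protocol estimate is kept, label it non-randomised and exploratory, and report the number excluded.

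The cost is a change of wording. The attendance data are those the present definition already needs. The drawback is a wider confidence interval than the naive per-protocol one, by a factor of about 1.2 at an assumed 75% attendance. On complete cases, the new estimate also carries the same missing-data assumption as the primary analysis.

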### Qualitative interviews

A sub-sample of participants in the intervention arm will be invited to take part in a qualitative interview about their experience of attending the Baby Steps programme and, in particular, of using the mobile web application that is part of the programme. Participants will be selected so that both those who do and those who do not engage with the application are interviewed. The interviews will include a discussion on whether the programme meets the social and cultural needs of the women. If the programme is shown to be effective in achieving our primary and secondary outcomes, then this qualitative information may be used to make revisions to the content or mode of delivery of the programme before it is offered to women outside a trial setting.

Soon after attending the 12 month follow-up clinic, selected participants will be invited to take part in a focus group, face-to-face interview or telephone interview (format will be the choice of the participant). Informed consent will obtained by the interviewer before the interview starts. Interviews will be digitally recorded unless the participant does not consent to the recording in which case notes will be made. Interviews will be carried out by an experienced researcher from the University of Leicester following an approved topic guide and then transcribed by a transcription service approved by the sponsor. A purposive sampling strategy will be used to ensure that a cross-section of participants is selected (for example, women from both sites, women who did and did not engage with the application) and it is anticipated that about 15–20 women will be interviewed. Interview data will be analysed through thematic analysis where information will be put into themes and a codebook produced, placing important emphasis on letting the themes emerge from the empirical data. This is the basis of grounded theory and thus there will be an explicit focus on open coding and development of themes as data is collected. Although themes will be based on the initial topic guide, data collection and data analysis will be flexible in nature and adopt a constant comparative approach. To aid structure in analysis because transcripts and qualitative data can be voluminous, research software packages such as Nvivo 10 will be used.

### Data management and monitoring

The Chief Investigator is responsible for ensuring that the study is conducted in full conformity with the current revision of the Declaration of Helsinki and with the ICH Guidelines for Good Clinical Practice (CPMP/ICH/135/95, July 1996). The participants’ anonymity is maintained at all points. Participants are identified only by an ID number and their initials on the CRF and any electronic database. All documents and patient identifiable information are stored securely in locked cabinets and on a password-protected computer or in off-site archiving rooms (according to the sponsor’s SOPs). The study complies with the general data protection regulation which requires data to be anonymised or pseudo-anonymised as soon as it is practical to do so. All data are entered on a validated electronic database which only includes the participant’s ID number and is stored for ten years and then archived according to the sponsor’s SOP. Any identifiable personal data will be permanently deleted from the servers once the final report has been submitted or within five years if the participant has agreed to be contacted for other studies.

As this is a minimal risk study, a Data Monitoring Committee has not been convened. Serious adverse events (SAE) are monitored and reported in line with requirements. An internal group meets every month to review recruitment rate, drop out, issues concerning delivery of the intervention and SAEs. A quarterly report on progress is submitted to the funder.

## Discussion

The National Institute for Health and Care Excellence (NICE) guidelines on diabetes in pregnancy recommend that women who have been diagnosed with GDM are offered a fasting plasma glucose or HbA1c test at 6–13 weeks postnatally, given lifestyle advice (including weight control, diet and exercise) and offered an annual HbA1c test [1]. It also recommends that women with an HbA1c of 39–47 mmol/mol (5.7% and 6.4%) are advised that they are at a high risk of developing T2D and should be offered advice, guidance and interventions in line with available guidelines to prevent T2D. The American Diabetes Association guidelines also recognises the high risk of T2D in this group and recommends women with GDM to have a 75 g oral glucose tolerance test (OGTT) at 4–12 weeks postpartum followed up by additional testing every 1–3 years if the OGTT is normal [53].

Primary care provision of postnatal care to this group is disappointing with annual rates of long-term follow-up of GDM in primary care only around 20% [54]. There is a need to improve the postnatal monitoring of women who have had GDM as well as to provide innovative ways to reduce progression from GDM to T2D.

The Baby Steps programme will aim to address these issues in a RCT with the primary outcome of improving physical activity levels at 12 months. The latter has been previously shown to be independently associated with reduction in risk of T2D and cardiovascular events in high-risk individuals [18, 30]. This robust programme has been developed following a large element of PPI work with input provided by women who have had GDM as well as healthcare professionals who work with this patient group. It is designed to accommodate the family and work commitments of women who have young children and the qualitative interview component of the study will evaluate the perception of the programme by service users who have different levels of engagement.

An important aspect of the programme is the mobile health technology which complements the group education sessions and is being used increasingly in several disciplines in medicine. Smart phones and wearable devices have the potential to improve public health and have shown some success in health behaviour change interventions [55–57]. These new technologies could shift the need from intensive face-to-face intervention towards an interactive, self-directed, personalised and cost-effective tool for women following a diagnosis of GDM. Mobile technology has been used in the management of GDM and the present study will add to this by investigating whether it has a role in the prevention of T2D in women with a history of GDM [58, 59].

The Baby Steps programme, if shown to be effective, could be delivered in a variety of settings, including primary care, to high-risk women from multi-ethnic populations and help reduce incidence of future T2D. The trial is restricted to women who are able to speak English, which limits our ability to meet all the language and cultural needs of a population with ethnic minorities. However, our team has a good track record of delivering similar lifestyle interventions in other languages. Therefore, if the findings from the study and qualitative interviews are positive, it may be possible to conduct the sessions in other languages in future to increase uptake among ethnic minority populations and target women with the highest risk of T2D.

### Trial status

Recruitment started on 5 April 2017 and is ongoing.

### Protocol version

The current protocol version is Version 5; 25 May 2018. Four substantial amendments have been approved. Amendment 1 (before recruitment started) involved a change in the randomisation procedure (from an online software system to manual allocation using a randomisation schedule). Amendment 2 involved making telephone calls to non-responders. Amendment 3 involved a change in eligibility criteria (from recruited within 36 months of most recent delivery to recruited within 60 months of any delivery). Amendment 4 involved carrying out qualitative interviews with participants from the intervention arm.

## Abbreviations

API: Human application programming interface
CRF: Clinical record form
ENMO: Euclidean Norm minus 1 *g*
EQ-5D-5 L: Health Related Quality of Life EuroQoL
FACET: Five-A-Day Consumption and Evaluation Tool
GDM: Gestational diabetes
HADS: Hospital Anxiety and Depression Scale
HDL: High-density lipoprotein
IGT: Impaired glucose tolerance
LDL: Low-density lipoprotein
LGA: Large for gestational age
NICE: National Institute for Health and Care Excellence
PIL: Patient information leaflet
PPI: Patient and public involvement
RCT: Randomised controlled trial
RPAQ: Recent Physical Activity Questionnaire
SAE: Serious adverse event
SOP: Standard operating procedure
T1D: Type 1 diabetes
T2D: Type 2 diabetes
